### Strategies to improve adherence to interventions {11c}

Drug accountability measures and patient diaries are implemented to improve protocol adherence. To avoid protocol violations due to dyspeptic and/or reflux symptoms after sudden discontinuation of PPI in the intervention group, patients undergo PPI dose tapering. Dyspepsia or symptomatic gastroesophageal reflux disease may be treated with sucralfat. Study participants are reminded to take study medication from the “study medication package” from day 15 on during a telephone interview on day 14.

### Relevant concomitant care permitted or prohibited during the trial {11d}

Open-label PPIs, h2-receptor antagonists and nelfinavir are prohibited during this trial (exception: rescue PPI therapy for up to 72 h in patients with suspected upper gastrointestinal bleeding events or peptic ulcers). Non-steroidal anti-inflammatory drugs (other than acetylsalicylic acid up to 100 mg/day) for more than 7 days during a period of 28 days are not permitted. Treatment with sucralfat for dyspepsia or symptomatic reflux disease is permitted.

### Provisions for post-trial care {30}

After completion of the trial, participants will be treated according to the current guidelines in the respective trial centres. All study participants are provided with an insurance to cover trial-related medical issues.

### Outcomes {12}

The primary composite endpoint is the time to unplanned re-hospitalizations or death during the trial period. However, expected re-hospitalization for mere paracentesis (without other complication of cirrhosis) during a period of 30 days after discharge is not regarded as an “unplanned re-hospitalization”. If the local investigator and the clinical trial management come to a conflicting assessment whether a re-hospitalization was “planned” or “unplanned”, a blinded endpoint committee (consisting of three independent hepatologists) will resolve this disagreement.

Secondary endpoints are described in Table 2. Importantly, patients who reach the primary endpoint “re-hospitalization” will continue all study procedures and will further receive the study medication. Therefore, secondary endpoints will be studied after a study participant has reached the primary endpoint. Patients who reach the safety endpoint (evidence-based re-therapy with PPI; see Table 2) are censored at the respective time-point.

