Thus, current evidence, even if not unambiguous, suggests an unfavourable risk profile of PPI in patients with liver cirrhosis. However, this patient population is considered to be at a high risk of gastrointestinal haemorrhage from peptic ulcers [37–40]. Importantly, peptic ulcer bleeding in patients with liver cirrhosis is associated with an increased mortality as compared to patients without cirrhosis [41–43], and mortality rates of cirrhotic patients with peptic ulcer bleeding are comparable to cirrhotic patients with bleeding from oesophageal varices [44]. Therefore, generous PPI use may also have a yet unproven preventive effect against upper gastrointestinal bleeding events. Short term use of PPIs for up to 10 days may reduce ulcer size after endoscopic variceal band ligation [45, 46], but there is no evidence for protective effects of PPI therapy against portal hypertension-related bleeding in cirrhotic patients who did not receive endoscopic ligation therapy [47].

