### Criteria for discontinuation or modifying allocated interventions {11b}

Patients who reach the safety endpoint (“evidence-based indication for re-therapy with PPI”; Table 2) will discontinue study medication. However, in case of clinically suspected peptic ulcer disease or signs of upper gastrointestinal haemorrhage rescue PPI treatment is permitted for up to 72 h or until an oesophago-gastro-duodenoscopy (EGD) is performed. If the EGD does not reveal a safety endpoint, rescue PPI therapy will be stopped and the patient continues study medication.

**Table 2 Tab2:** Primary, secondary and safety endpoints of the trial

Primary composite endpoint	Secondary endpoint
1.) Unplanned re-hospitalization	1.) Death
2.) Death	2.) Unplanned re-hospitalization
	3.) Any infection and differentiated by site of infection (SBP, pneumonia, urinary tract infection, blood stream infection, Clostridium difficile-associated enterocolitis, Norovirus infection, SARS-CoV-2 infection, others)
	4.) Acute hepatic decompensation and ACLF
	5.) Upper or lower gastrointestinal bleeding event
	**Safety endpoint:** Evidence based re-therapy with PPI due to the occurrence of any the following conditions:
	1.) Peptic ulcer diagnosed by EGD
	2.) Reflux esophagitis LA grade C or D diagnosed by EGD
	3.) Severe hemorrhagic gastritis diagnosed by EGD and histology
	4.) Mallory-Weiss syndrome diagnosed by EGD

*SBP* spontaneous bacterial peritonitis, *SARS-CoV-2* severe acute respiratory syndrome coronavirus 2, *ACLF* acute-on-chronic liver failure, *PPI* proton-pump inhibitors, *EGD* oesophago-gastro-duodenoscopy

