### Plans to promote participant retention and complete follow-up {18b}

If possible, complete follow-up data should be obtained from all patients. Investigators motivate trial participants to attend all study visits. Patients who discontinue the investigational product will attend all subsequent study visits, in which endpoint data will be collected. The primary efficacy analysis will follow intention-to-treat principles.

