## Statistical methods

### Statistical methods for primary and secondary outcomes {20a}

The primary efficacy endpoint analysis will be performed according to the intention-to-treat (ITT) principle based on the full analysis set (FAS). The effects of continuation or discontinuation of PPI therapy with respect to the primary endpoint will be estimated and tested by Cox regression. The regression model will include treatment arm and categorized the severity of cirrhosis (MELD ≤ 13 vs. > 13) as fixed effects and the study centre as a random effect. As an estimated effect size, the hazard ratio (HR) between the two treatment arms will be given with the corresponding 95% confidence interval. The one-sided test of the superiority of discontinuation of PPI over the continuation of PPI at significance level 2.5% will be based on the corresponding asymptotic two-sided 95% confidence interval from the Cox regression model. The null hypothesis is rejected if the upper limit of the confidence interval is below 1.0. The analysis of the treatment effect with respect to the individual components of the composite endpoint and to secondary endpoints will be performed analogously with the (cause-specific) Cox model. Time to event outcomes will be visualized by Kaplan-Meier curves stratified by treatment group. Adverse event data will be summarized by the treatment group.

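### Censoring at the safety endpoint conflicts with the intention-to-treat primary analysis, has no stated scope, and may tilt the comparison modestly towards discontinuation

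*Protocol article*

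**What the plan says.** Four parts of the protocol article bear on this.

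- **Outcomes {12}:** "Patients who reach the safety endpoint (evidence-based re-therapy with PPI; see Table 2) are censored at the respective time-point". The sentence closes a paragraph on secondary endpoints. It does not say whether it applies to the primary composite, to time to death, or to every time-to-event analysis.
- **Criteria for discontinuation {11b} and Table 2:** patients who reach the safety endpoint "will discontinue study medication". All four qualifying conditions need an endoscopic finding; the first is "Peptic ulcer diagnosed by EGD".
- **Retention and follow-up {18b}:** "Patients who discontinue the investigational product will attend all subsequent study visits, in which endpoint data will be collected". The same section adds: "The primary efficacy analysis will follow intention-to-treat principles".
- **Statistical methods {20a}:** the primary analysis is again intention-to-treat, on the full analysis set, by Cox regression. Success requires the upper 95% confidence limit of the hazard ratio to lie below 1.0.

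Section {20c} treats dropout as independent right censoring and names sensitivity analyses for substantial dropout. It does not mention censoring at the safety endpoint.

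**The concern.** An intention-to-treat time-to-event analysis counts a patient's events whether or not study drug has been stopped. The censoring sentence instead ends a patient's contribution when a reason to restart PPI is found. The sites will hold the later data, but an analyst following {12} would not use them, while one following {18b} and {20a} would.

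The trigger is not neutral. It is an outcome after randomisation that treatment may influence. The Background {6a} allows that PPI may protect against upper gastrointestinal bleeding, though it calls this unproven, and states that "peptic ulcer bleeding in patients with liver cirrhosis is associated with an increased mortality as compared to patients without cirrhosis". The Abstract's discussion lists more bleeding after withdrawal as a possible result of the trial. If safety endpoints are commoner on placebo and the patients concerned then do worse, censoring removes higher-risk follow-up mainly from the placebo arm. The error would favour the hypothesis that the trial sets out to prove.

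**Working it through.** **1. The plan's own figure.** From 50% and 65% event rates at 6 months (Sample size {14}), HR = ln(0.50)/ln(0.35) = 0.660. With 1:1 allocation, two-sided 5% and 80% power:

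- Schoenfeld: 4 × (1.960 + 0.842)² / (ln 0.660)² gives 183 events.
- Freedman: (1.960 + 0.842)² × (1.660/0.340)² gives 188 events.
- The plan states 184, at which Schoenfeld power is 80.4%.

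The figure is reproduced. With constant hazards and no loss to follow-up, day-360 event risks are 1 − 0.50² = 75% and 1 − 0.35² = 87.75%. That is 238 × (0.75 + 0.8775) ≈ 387 events among 476 patients. Nothing here depends on the censoring rule.

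**2. What the rule removes.**

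- *Primary composite (first event).* A patient admitted unplanned before the endoscopy already has the event, so nothing is lost. What is lost is a first unplanned admission or death after a safety endpoint found without a prior unplanned admission. Admission and endoscopy on the same day have no tie rule.
- *Time to death.* If the sentence applies, every death after the safety endpoint is lost, whatever the route to endoscopy.

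**3. Size.** The documents give no safety-endpoint rate and no prognosis after it, so these are assumptions: day-360 risks (control/withdrawal) of 2%/5%, 3%/10% and 5%/15%; hazard multiplied by 2 or 4 after the safety endpoint; constant hazards; no other loss. Cox hazard ratios come from large simulated samples and vary by about 0.003 between runs.

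Primary composite, with no safety endpoint preceded by an unplanned admission:

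| Safety endpoint | Hazard after | Design HR 0.66: all events counted | Censored | No other effect: all events counted | Censored |
|---|---|---|---|---|---|
| 2%/5% | ×2 | 0.668 | about 0.66 | 1.007 | 1.001 |
| 2%/5% | ×4 | 0.671 | about 0.66 | 1.010 | 1.000 |
| 3%/10% | ×2 | 0.675 | about 0.66 | 1.014 | 0.999 |
| 3%/10% | ×4 | 0.687 | about 0.66 | 1.023 | 0.998 |
| 5%/15% | ×2 | 0.678 | about 0.66 | 1.020 | 0.997 |
| 5%/15% | ×4 | 0.699 | about 0.66 | 1.038 | 1.001 |

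This is the least favourable timing. In the last row with no other effect, if half the safety endpoints present as an unplanned admission first, the values are 1.043 and 1.024, a gap of 0.019 instead of 0.037. If all do, the two analyses are identical.

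Time to death, no other treatment effect, assumed one-year mortality 20% or 30%:

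| Safety endpoint | Hazard after | All deaths counted (20% / 30%) | Censored (20% / 30%) |
|---|---|---|---|
| 2%/5% | ×2 | 1.015 / 1.011 | 1.002 / 0.997 |
| 2%/5% | ×4 | 1.032 / 1.032 | 0.997 / 1.001 |
| 3%/10% | ×2 | 1.030 / 1.028 | 0.999 / 0.997 |
| 3%/10% | ×4 | 1.084 / 1.074 | 1.001 / 1.001 |
| 5%/15% | ×2 | 1.049 / 1.043 | 1.002 / 1.000 |
| 5%/15% | ×4 | 1.117 / 1.105 | 1.001 / 0.999 |

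Per 476 patients, the deaths discarded range from 96.5 − 93.5 = 3 to 156.1 − 136.1 = 20.

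**4. When nothing moves.** With equal rates (5%/5%), or no change in hazard after the safety endpoint, the two analyses agree to within simulation error or a negligible amount.

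**The case against.** A reader might infer that the rule removes the main harm pathway of stopping PPI from the primary endpoint, and could so produce a false claim of benefit or safety. The documents do not support that.

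- A bleed that leads to an unplanned admission before endoscopy already counts as a primary event.
- The safety endpoint does not require bleeding: non-bleeding ulcers and severe oesophagitis qualify. The background sentence on mortality compares ulcer bleeding with and without cirrhosis, not cirrhosis with and without a safety endpoint. Unequal rates and worse prognosis are therefore possibilities, not facts.
- The article does not say that the rule covers mortality, and it stresses that secondary endpoints are followed after re-hospitalisation. The larger death figures depend on that reading.
- The primary shift is small against sampling error. With 387 events the standard error of log HR is 2/√387 = 0.102, so success needs an observed HR near exp(−1.96 × 0.102) = 0.82; with 184 events, near 0.75. The largest shift, ln(0.699/0.66) = 0.057, is a little over half a standard error. Where withdrawal has no other effect, the censored HR is about 1.00 and the chance of a false benefit claim stays near the nominal 2.5%.
- Harm is also seen through the safety endpoint itself, bleeding as a secondary endpoint, serious adverse event reporting and the unblinded DSMB.

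It is also fair that collecting data and censoring in one analysis are compatible. The conflict is with the intention-to-treat principle, not with data collection as such.

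All of this stands and limits the claim. None of it reconciles {12} with {18b} and {20a}, or supplies the missing scope and tie rule.

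**Conclusion.** The concern holds in a limited form. The article gives two incompatible rules for which events the primary analysis counts, and leaves open whether the censoring rule also governs mortality. This is more than detail left to an analysis plan, because both rules are stated.

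The bias is conditional. It needs safety endpoints to be commoner after withdrawal and to worsen prognosis, and it then favours discontinuation; no scenario tried moved materially the other way. Under the assumed ranges it is about 0.005-0.04 on the primary hazard ratio, at most, since that supposes no prior unplanned admission. It is about 0.01-0.12 on the death hazard ratio, if the rule applies there. The primary result is unlikely to be overturned unless it is borderline; mortality is more exposed.

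**What to change.** Replace the censoring sentence in {12}. For the primary composite and the mortality analyses, state that patients are followed to day 360 and that unplanned admissions and deaths count regardless of PPI re-therapy, as {18b} and {20a} already imply. Keep censoring at the safety endpoint only as a labelled supplementary analysis, naming the endpoints to which it applies. State that an unplanned admission on the same day as the endoscopy counts as an event.

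The cost is wording: the data are already to be collected, and 184 events and 476 patients are unchanged. The one statistical downside is slight dilution of the contrast from patients back on PPI. The clinical rule on stopping study drug is not affected. The change should be made before unblinding, because a later choice between the two rules could look data-driven.

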### Participant timeline {13}

Recruitment is planned to be completed within three years. With a trial duration 360 days per patient, time of first-patient-in to last-patient-out is four years. Figure 1 provides an overview of the trial design. After completion of the informed consent process, the screening visit will take place. Randomization will take place 0 to 14 days after screening during the baseline visit (visit 1, day 0). The study is split into two parts: “dose tapering phase” (days 1–14; tapering of the PPI dose in a blinded fashion, see above) and “main study phase” (days 15–360). Study visits and telephone interviews take place at the time-points indicated in Table 3. Study procedures during the respective visits and telephone interviews are summarized in Table 4.

**Table 3 Tab3:** Visits and time points

Screening visit	Up to 14 days before baseline
**Visit 1 (baseline)**	Day 0
**Visit 2**	Day 28 (± 2 days)
**Visit 3, 4, 5, 6**	Day 90, 180, 270, 360 (± 7 days, respectively)
**Telephone interview 1**	Day 14 (± 2 days)
**Telephone interview 2, 3**	Day 135, 225 (± 7 days, respectively)

**Table 4 Tab4:** Study procedures

Procedure	Screening	Baseline visit	Visits 2–6	Telephone interviews
Informed consent	X			
In-/exclusion criteria	X			
Randomization		X		
Medical history/demographics	X	X		
Adverse events/concomitant medication/endpoint assessment		X	X	X
Physical examination/height and weight		X	X	
Vital sign assessment	X	X	X	
Laboratory (haematology, biochemistry)		X	X	
Pregnancy test	X			
Stool samples & biobanking		X	X (visit 3)	
Ultrasound		X	X (visit 4, 6)	
Distribution and/or return of study medication and patients diaries		X	X	

### Sample size {14}

The sample size is based on the composite primary endpoint time to death from any cause or time to unplanned re-hospitalization from any cause. Based on previous studies on mortality in cirrhosis patients who receive PPI [5, 6, 10, 32, 33] and an assumed 50% risk for re-hospitalization 3 months after discharge in decompensated cirrhotic patients [20, 30, 50], it is expected that the control group will have a probability of 65% to reach the primary endpoint after 6 months. The risk to reach the primary endpoint in the PPI withdrawal group is assumed to be 50% after 6 months, due to a reduction of mortality [4–6, 8, 10, 11] and a decreased risk for infectious complications [8–10, 12–16], which results in a lower risk for re-hospitalization [20]. This corresponds to a HR of 0.66 of the intervention group compared to the control group. The sample size calculation is performed on the assumed event rates of 50% in the intervention group (PPI withdrawal) and 65% for the control group after 6 months with a two-sided significance level α of 5% and a power of 80%, which requires a total number of 184 events to be observed. With a follow-up period of exactly 360 days per patient and an estimated 20% random loss to follow-up or non-compliance it can safely be assumed that a sufficient number of events will have been observed by the end of the trial if a total of 475 patients are available for analysis (based on the log-rank test; PASS 16.0.3). Therefore, 476 patients will be randomized.

### Recruitment {15}

Patients will be recruited at the trial centres during or after hospitalization. Global and local recruitment rates will be monitored by the clinical project management and the data safety and monitoring board (DSMB). Trial sites are obliged to recruit a number of patients according to their respective pre-study prognosis. In case trial sites do not fulfil these obligations in a specified time, countermeasures can be taken (e.g., direct communication with the investigator, addendum to the protocol).

## Assignment of interventions: allocation

### Sequence generation {16a}

Randomization will be carried out locally. A block randomization procedure with variable block length will be applied stratified for the study centres and severity of liver cirrhosis (MELD score ≤13 or > 13). Blinding of therapy for the patients and the investigators will be ensured by identical encapsulation of placebo and esomeprazole 20 mg that makes both indistinguishable, and by the use of identical medication packages. Unique randomization codes labelled on the medication packages ensure the specific allocation of the study medication to the study participant.

### Concealment mechanism {16b}

Each centre has two randomization lists (MELD ≤13 and > 13). The lists include only the randomization numbers and do not reveal the study medication.

### Implementation {16c}

Only the Pharmacy of the University Medical Center Hamburg-Eppendorf performing the randomization procedure, and neither the investigators nor the study participants, will be aware of the allocation sequence or the block size used. Randomization numbers are allocated to patients sequentially by local study staff.

## Assignment of interventions: blinding

### Who will be blinded {17a}

Investigators, study participants, (clinical) trial management, data management, pharmacovigilance officers and data analysts are blinded. Only the central pharmacy and the data safety monitoring board (DSMB) members are unblinded.

### Procedure for unblinding if needed {17b}

Access to emergency envelopes is regulated at all trial sites. Details on the unblinding procedures are found in the investigator site files.

## Data collection and management

### Plans for assessment and collection of outcomes {18a}

Clinical outcome, baseline and other trial data will be collected during the visits and telephone interviews (Table 4) at the time points detailed in Table 3. Site staff will transfer trial data from the source documents into the electronic case report form (eCRF) and check eCRF entries for completeness. Corrections to source data or eCRF data will be dated and signed. Reasons for changes must be provided. Source data verification will take place during on-site monitoring. To initiate discrepancy resolution the monitor will send queries to the site staff.

### Plans to promote participant retention and complete follow-up {18b}

If possible, complete follow-up data should be obtained from all patients. Investigators motivate trial participants to attend all study visits. Patients who discontinue the investigational product will attend all subsequent study visits, in which endpoint data will be collected. The primary efficacy analysis will follow intention-to-treat principles.

### Data management {19}

Data management will check predefined eCRF entries as defined in the data validation plan. Quality control and data validation procedures such as programmed automatic edit and consistency checks ensure data validity and accuracy immediately at the point of entry into the clinical database. The database application is an access restricted, demands electronic signatures, maintains an electronic audit trail and provides appropriate backup functionalities.

### Confidentiality {27}

Data obtained during the trial will be treated pursuant to the Federal Data Protection Law. Subjects will be identified solely by their individual randomization number. Trial data stored on a computer will be stored in accordance with local data protection law and will be handled in the strictest confidence. The appropriate regulations of local data legislation will be fulfilled in its entirety.

### Plans for collection, laboratory evaluation and storage of biological specimens for genetic or molecular analysis in this trial/future use {33}

Blood and urine samples will be collected for biobanking and further analysis in the future. Patients may choose not to provide these optional biobanking samples.

## Statistical methods

### Statistical methods for primary and secondary outcomes {20a}

The primary efficacy endpoint analysis will be performed according to the intention-to-treat (ITT) principle based on the full analysis set (FAS). The effects of continuation or discontinuation of PPI therapy with respect to the primary endpoint will be estimated and tested by Cox regression. The regression model will include treatment arm and categorized the severity of cirrhosis (MELD ≤ 13 vs. > 13) as fixed effects and the study centre as a random effect. As an estimated effect size, the hazard ratio (HR) between the two treatment arms will be given with the corresponding 95% confidence interval. The one-sided test of the superiority of discontinuation of PPI over the continuation of PPI at significance level 2.5% will be based on the corresponding asymptotic two-sided 95% confidence interval from the Cox regression model. The null hypothesis is rejected if the upper limit of the confidence interval is below 1.0. The analysis of the treatment effect with respect to the individual components of the composite endpoint and to secondary endpoints will be performed analogously with the (cause-specific) Cox model. Time to event outcomes will be visualized by Kaplan-Meier curves stratified by treatment group. Adverse event data will be summarized by the treatment group.

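### The primary Cox model adjusts for MELD only as ≤13 vs >13; adding the numeric score that stratification already requires would be a cheap, modest gain in efficiency

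*Protocol article*

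**What the plan says.** Protocol article, Statistical methods for primary and secondary outcomes {20a}, on the primary Cox model: "The regression model will include treatment arm and categorized the severity of cirrhosis (MELD ≤ 13 vs. > 13) as fixed effects". Centre enters as a random effect. The components of the composite and the secondary endpoints are to be analysed in the same way with cause-specific Cox models, so the choice carries through.

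Sequence generation {16a}: randomisation is "stratified for the study centres and severity of liver cirrhosis (MELD score ≤13 or > 13"). Concealment mechanism {16b}: "Each centre has two randomization lists (MELD ≤13 and > 13"). The model therefore adjusts for exactly the two stratification factors.

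Participant timeline {13}, Table 4: the row "Laboratory (haematology, biochemistry") is marked at the baseline visit, where randomisation also takes place.

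Sample size {14}: the calculation uses "assumed event rates of 50% in the intervention group (PPI withdrawal) and 65% for the control group after 6 months". Target power is 80% at a two-sided α of 5%. The method is the log-rank test, which takes no credit for covariates.

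**The concern.** A list cannot be chosen at randomisation without a MELD score, yet the analysis keeps only which side of 13 the patient falls on. A patient with MELD 14 and one with MELD 30 are given the same baseline risk. In a Cox model, prognostic variation left out of the model pulls the treatment hazard ratio towards 1 and costs power, even under perfect randomisation.

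What is at stake is efficiency, not validity. It would matter most if the true effect is weaker than the planned hazard ratio of 0.66. That is plausible: the article's Background and Discussion describe the supporting evidence as observational and conflicting.

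**Working it through.** **1. The plan's own figure.** From Sample size {14}: 6-month risks of 65% and 50%, two-sided α 5%, power 80%, 184 events.

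- HR = ln 0.50 / ln 0.35 = 0.660.
- Schoenfeld: 4(1.960 + 0.842)² / (ln 0.660)² = 182.2, so 183 events. Freedman: 188. The stated 184 is reproduced; at HR 0.66 it gives 80.5% power.
- The analysis test ("The one-sided test of the superiority of discontinuation of PPI over the continuation of PPI at significance level 2.5"%, read from a two-sided 95% interval) is equivalent for superiority.

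**2. Information kept by the cut.** This is the squared correlation between the binary and the numeric score. For a normal score it is φ(c)² / [p(1 − p)], where p is the proportion below the cut and c the matching normal quantile.

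| Assumed score | Kept | Lost |
|---|---|---|
| Normal, cut at median | 64% | 36% |
| Normal, 30/70 split | 58% | 42% |
| Normal, 20/80 split | 49% | 51% |
| Skewed, mean 13, SD 5 | 63% | 37% |
| Skewed, mean 14, SD 5.5 | 60% | 40% |
| Skewed, mean 15, SD 6 | 56% | 44% |
| Skewed, mean 17, SD 6 | 46% | 54% |

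The skewed rows use the cut at 13. A normal score with mean 15 and SD 4.2 keeps 59% (cut at 13) or 61% (cut at 13.5). More than half is lost only if the cut is well off-centre.

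**3. Power at the planned effect.** Simulation of 3,000 trials per row: 476 patients 1:1, exponential times, marginal 6-month risks held at 65%/50%, 20% dropout per year, skewed MELD (mean 14, SD 5.5). Power at 184 events:

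| MELD HR per SD | No MELD | Binary | Linear | Linear − binary |
|---|---|---|---|---|
| 1.0 | 80.0% | 79.8% | 79.9% | 0.1 |
| 1.2 | 80.9% | 81.0% | 81.1% | 0.1 |
| 1.35 | 80.7% | 81.7% | 82.9% | 1.2 |
| 1.5 | 81.4% | 83.4% | 85.1% | 1.7 |
| 1.75 | 82.6% | 85.8% | 88.1% | 2.3 |
| 2.0 | 83.1% | 87.4% | 91.4% | 4.0 |

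Here the linear term replaces the binary one. At full 360-day follow-up (about 344–358 events) both models reach 98–99.5%, and the gap is at most 0.8 points.

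**4. Power if the effect is weaker.** Conditional HR 0.75, full follow-up, control 6-month risk 65%, 20% loss, MELD mean 15, SD 4.2. Binary MELD alone is compared with binary plus continuous MELD:

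| MELD HR per point | Run of 2,000 trials | Run of 1,500 trials |
|---|---|---|
| 1.05 | 77.1 → 78.0% (+0.9) | 78.0 → 78.7% (+0.7) |
| 1.11 | 74.0 → 77.6% (+3.6) | 75.1 → 78.4% (+3.3) |
| 1.16 | 69.4 → 77.2% (+7.8) | 71.4 → 77.1% (+5.7) |

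With skewed MELD (SD 5.5) and 1.11 per point, the gain is 71.8 → 76.8% (+5.0) at mean 14 and 70.0 → 77.0% (+7.0) at mean 17. A further run of 1,500 trials gave gains of 0, 6 and 8 points for the three MELD effects, from a lower base (65–74%). Its baseline hazard is not recorded, so I give it less weight.

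In the 2,000-trial run the binary model's estimated HR drifted to 0.750, 0.758 and 0.766; with the continuous term it stayed at 0.75. With the conditional HR set to 0.66, the gains were 0.2, 0.9 and 2.5 points (2,000-trial run), 0, 2 and 2 (1,500-trial run) and 0, 1 and 4 (further run).

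**5. Type I error.** At HR 1.0 the one-sided error was 2.2–2.8% in both models.

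Monte Carlo error is about 1 point or less throughout. The random centre effect was omitted from the runs in steps 3 and 4 for which the set-up is fully recorded.

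**The case against.** The best defence is that nothing here is an error. Adjusting for the stratification factors, at the same cut and with centre included, is a sound pre-specified analysis, and a richer covariate model is a matter of preference. That stands as to validity. It does not remove the case for a cheap improvement to a model that the article itself fixes.

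A reader might infer that the cut discards most of the prognostic information. The documents do not support this: they give no MELD distribution, and a cut near the centre keeps roughly 55–65%.

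A reader might also infer that the trial is underpowered as a result. It is not. The 80% was set without covariate help, and the binary model delivers 80–87% at 184 events.

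It is also fair to say that the larger gains need both a hazard ratio that is not the design value and a strong MELD effect: 1.11–1.16 per point is 1.11^4.2 = 1.55 to 1.16^4.2 = 1.87 per SD. The composite includes re-hospitalisation from any cause, and nothing in the documents says how well MELD predicts that. All simulations made the effect exactly log-linear, which favours the proposed term.

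**Conclusion.** The point holds as a minor efficiency suggestion. The stratum-adjusted model is valid, but it forgoes some precision by leaving out a substantial part, roughly 35–45% for a cut near the centre, of the information in a score the trial already needs.

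The forgone power is about 0–4 points at HR 0.66 and about 1–8 points at HR 0.75, falling to little or nothing if MELD is a weak predictor of the composite. These figures depend on assumed MELD distributions and effects, and they sit on the high side.

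That the numeric score exists for every patient is inferred from the two lists per centre; the article does not say outright that the value is recorded.

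**What to change.** Pre-specify baseline MELD as a continuous term in the primary and secondary Cox models, with one stated functional form (linear, for example) rather than a choice left open. Keep the MELD stratum indicator and the random centre effect. Name which MELD value is meant, sensibly the one used to select the randomisation list. Report the currently specified model as a sensitivity analysis. Settle this before any unblinding and before the interim futility look, which depends on the treatment p-value.

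The cost is wording: no new patients or visits. Under the article's amendment rules {25}, the sponsor would have to decide whether the change counts as substantial. One small statistical downside should be stated in the report: the hazard ratio becomes conditional on MELD value and may lie slightly further from 1 than the stratum-adjusted one.
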